### Sample size calculations

Aim of the trial is to demonstrate non-inferiority of magnesium-based compression screws when compared with titanium Herbert screws for the fixation of scaphoid fractures. Standard deviations (SD) for the PRWE in the literature were all approximately 20 points [47]. Lange and Freitag [48] reported in their systematic review that many studies used a non-inferiority margin of 0.5 SD. This limit is used a non-inferiority margin for the planning of the scaphoid trial for the primary endpoint PRWE. This leads to the following assumptions for the sample size calculations for the first primary endpoint: Allocation ratio 1:1, type I error level 0.025 one-sided, power 0.9, expected difference between titanium and magnesium-based screws: Δ_1_ = 0, common standard deviation: σ = 20, non-inferiority margin: Δ_0_ = 10, drop-out 10%. To demonstrate non-inferiority under these assumptions, 94 patients per group, i.e., 188 patients in total are required for this trial.

If non-inferiority has been established for the first primary endpoint, the power to establish non-inferiority for the second primary endpoint, the safety endpoint is 90.64% under the following assumptions: type I error level 0.025 one-sided, event rate for magnesium-based and titanium screws: 0.9, non-inferiority margin: Δ_0_ = 0.15, drop-out 10%.

If non-inferiority has been established for the first primary endpoint and the second primary endpoint, the power to establish superiority for the third primary endpoint, the change in artifacts endpoint is virtually 100% under the following assumptions: type I error level 0.025 one-sided, expected difference between titanium and magnesium-based screws: Δ_1_ = 3.0, common standard deviation: *σ* = 1.0, sample size per group: *n*_*A*_ = *n*_*B*_ = 10, drop-out 10%, effective sample size per group: *n*_*A*_ = *n*_*B*_ = 9. The power is 56.41% if the mean difference is Δ_1_ = 1.0 instead of Δ_1_ = 3.0, and it is approximately 80% for Δ_1_ = 1.32.

The expected difference between the titanium and the magnesium-based group are substantiated as follows. Mean ± standard deviation artifact size were 8.4 ± 0.7 mm in the magnesium group and 12.9 ± 1.0 mm in the titanium group in the work of Sonnow et al. [15]. We assume a random reduction in artifact size in the titanium group of 1.0 mm and a halving of the artifact size in the magnesium group so that the difference is 3.4 mm, which is rounded to 3 mm. Due to the lack of additional data, we assume a common standard deviation of 1 mm, which is the standard deviation in the titanium group.

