### Statistical analysis

All statistical analyses will be described in detail in a statistical analysis plan (SAP) which will be finalized before the randomization of the last patient. Analysis populations for the primary endpoints will be the full analysis set (FAS) based on the intention to treat (ITT) principle and the per protocol population (PP). Neither interim analyses nor adaptations are planned for this trial. All statistical analyses will be done using the R software.

The familywise error rate is set to 5%. The three primary hypotheses will be investigated hierarchically.

The hypothesis for the first primary endpoint is that the mean PRWE in the magnesium-based group is non-inferior to the mean PRWE in the titanium group, measured 6 months after randomization. The non-inferiority margin is 10 points; low values of the PRWE denote ‘no pain’ or ‘no difficulty’. The one-sided 97.5% confidence interval from the t-test will be estimated for judging non-inferiority. Sensitivity analyses will be performed using linear mixed models with center as random effect.

The hypothesis for the second primary endpoint is that the rate of safety events in the magnesium-based group is non-inferior to that in the titanium group within 1 year after surgery. The non-inferiority margin is 15%. The one-sided 97.5% Wilson score interval for the difference of two proportions will be estimated for judging non-inferiority [45]. Sensitivity analyses will be performed using logistic regression mixed models with center as random effect.

The type I error level is set to 2.5% one-sided for the first two primary endpoints. Non-inferiority will only be claimed ifthe hypothesis for the first primary endpoint shows non-inferiority in the FAS based on the ITT population,the hypothesis for the second primary endpoint shows non-inferiority in the FAS based on the ITT population,the hypothesis for the first primary endpoint shows non-inferiority in the PP population andthe hypothesis for the second primary endpoint shows non-inferiority in the PP population.

No adjustments will be made for multiple testing because both tests need to demonstrate non-inferiority.

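### The 90.64% safety power does not describe the planned Wilson-type interval (about 88%), its event rate is mislabelled, and the power of the two-endpoint claim is not stated

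*Protocol article*

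**What the plan says.** All references are to the protocol article.

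- **Sample size calculations, PRWE.** The trial is sized on the first primary endpoint alone: "Allocation ratio 1:1, type I error level 0.025 one-sided, power 0.9, expected difference between titanium and magnesium-based screws" of zero, with "common standard deviation: σ = 20", a margin of 10 points and 10% drop-out. The result is 94 per group, 188 in total.
- **Sample size calculations, safety.** Given success on the first endpoint, "the power to establish non-inferiority for the second primary endpoint, the safety endpoint is 90.64% under the following assumptions". The assumptions are "type I error level 0.025 one-sided, event rate for magnesium-based and titanium screws: 0.9, non-inferiority margin" 0.15, and 10% drop-out. No effective sample size is given for this endpoint.
- **Statistical analysis, safety.** The hypothesis concerns the rate of safety events. "The non-inferiority margin is 15" percent, and "The one-sided 97.5% Wilson score interval for the difference of two proportions will be estimated for judging non-inferiority".
- **Primary endpoints.** A patient scores 1 for a safety event after an adverse device effect in surgery or wound healing, a serious adverse device effect, a reoperation, or lack of union by 6 months.
- **Statistical analysis, claim rule.** Non-inferiority requires success on PRWE and on safety, each in the FAS and in the PP population. The multiplicity statement rests on this: "No adjustments will be made for multiple testing because both tests need to demonstrate non-inferiority". The MRI superiority test follows only after that claim.

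**The concern.** A power quoted to two decimals should belong to the analysis that will be run. Here the declared analysis is a Wilson-type interval, which behaves differently from a Wald interval when proportions are near 0.1 or 0.9, so the two need not have the same power.

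The rate assumption also conflicts with the endpoint definition. Read literally, 90% of patients in each arm would have a safety event.

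Finally, requiring two endpoints to succeed protects the type I error but costs power. The sample size section gives one figure per endpoint and none for the rule that decides whether non-inferiority is claimed. A reader who wants the trial's chance of meeting its stated aim cannot find it, and the same unstated probability governs how often the MRI test is reached.

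**Working it through.** **Inputs.** From Sample size calculations: 94 per group, 10% drop-out, one-sided 0.025, rate 0.9 in both arms, safety margin 0.15; PRWE SD 20, margin 10, true difference 0. From Statistical analysis: Wilson score interval for safety, t-test interval for PRWE, both endpoints required. Evaluable per group: 94 × 0.9 = 84.6, so 84 to 85.

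**1. Reproducing 90.64%.** The Wald formula with unpooled variance is Φ(0.15 / √(2 × 0.1 × 0.9 / n) − 1.96). At n = 86, √(0.18/86) = 0.04575, 0.15/0.04575 = 3.279, and Φ(1.319) = 0.9064, an exact match. At n = 84.6 the same formula gives 0.9018. The stated MRI power of 56.41% is likewise a normal-approximation value (n = 9, difference 1, SD 1: 0.5641), so normal approximations appear to have been used elsewhere in the section too.

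**2. Power of the planned interval.** I take the Wilson interval for a difference to be the Newcombe type without continuity correction. Let p1 and p2 be the observed event proportions for magnesium and titanium, u1 the upper Wilson limit for p1 and l2 the lower Wilson limit for p2. Non-inferiority is shown if

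(p1 − p2) + √((u1 − p1)² + (p2 − l2)²) < 0.15.

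Summing the binomial probabilities of all outcomes that meet this, with a true rate of 0.1 in both arms:

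| Evaluable per group | Wald approximation | Wilson-type interval, exact |
|---|---|---|
| 84 | 0.8998 | 0.8785 |
| 85 | 0.9031 | 0.8761 |
| 86 | 0.9064 | 0.8869 |

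The slight drop from 84 to 85 is due to discreteness. With 84 in one arm and 85 in the other, the values are 0.874 and 0.877. A continuity-corrected version would be lower (0.831 at 84, 0.845 at 85).

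**3. The rate label.** The variance term is 0.9 × 0.1 = 0.09 whether the rate is 0.9 or 0.1. With equal rates in equal arms the power is the same, so the error lies in the label and not in the number.

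**4. Power of the two-endpoint claim in the FAS.** PRWE power from the noncentral t is 0.8965 at n = 84 and 0.8999 at n = 85. At n = 85, with safety power 0.8761:

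- independence: 0.8999 × 0.8761 = 0.788 (also 0.788 at n = 84);
- correlation between the test statistics of 0.3, 0.5 and 0.7 (bivariate normal): 0.802, 0.814 and 0.829;
- any dependence: from 0.8999 + 0.8761 − 1 = 0.776 up to the smaller of the two powers, 0.876 (0.8785 at n = 84).

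The article's own two figures, multiplied, give 0.90 × 0.9064 = 0.816.

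**The case against.** **The article never says the combined claim has 90% power.** This stands. A reader might infer it, since every figure for the two non-inferiority endpoints is 90% or more. But 0.9 belongs to PRWE alone, and the safety and MRI powers are worded as conditional on the preceding steps. The fault is a missing figure, not a false one.

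**On the conditional wording, 90.64% might be right.** Dividing joint power by PRWE power at n = 85 gives 0.8017/0.8999 = 0.891, 0.8136/0.8999 = 0.904 and 0.8294/0.8999 = 0.922 for correlations of 0.3, 0.5 and 0.7. A conditional power near 90.64% is therefore possible. However, no correlation is among the listed assumptions, and the exact Wald match points to an unconditional calculation.

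**The match at 86 per group is not a sample-size error worth pursuing.** This stands. Wald power at 84 to 85 is 0.900 to 0.903, under one point from the stated figure. The abstract's approximate total of 190 gives 95 × 0.9 = 85.5, which may explain 86, though that is an inference. The change of method accounts for most of the gap.

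**Planning with a normal approximation is common, and three points decide nothing.** In part. The 94 per group comes from PRWE alone, so no design decision depends on the safety figure. A power given to two decimals should still match the declared analysis.

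**The evaluable number is uncertain, because missing primary outcomes will be imputed.** This also stands in part. If all 94 per group counted as fully observed, safety power would be 0.915 and joint power under independence 0.848. But the article's own power statement assumes 10% drop-out, so 84 to 85 is the consistent basis.

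**Conclusion.** The point holds in limited form.

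- Under the planned interval, unconditional safety power is about 88%, roughly three points below the stated figure. This assumes a Newcombe-type interval without continuity correction, 84 to 85 evaluable per group and a true event rate of 0.1 in both arms.
- The rate of 0.9 is mislabelled: it is the event-free rate. No number changes.
- The power of the two-endpoint claim is not stated. In the FAS it is about 79% under independence, about 80% to 83% with test-statistic correlation of 0.3 to 0.7, and at most about 88% under any dependence.

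A flat 79% would say too much. It needs independence, which the article does not state, and non-union or reoperation plausibly worsens PRWE, which favours positive correlation. The PP requirement can only lower the power of the full claim, but the article gives no PP exclusion rate, so no figure for that reduction can be supported. Nor do these results show that the trial needs more patients.

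**What to change.** In Sample size calculations:

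1. State the assumed safety event rate as 0.1 per arm (event-free rate 0.9).
2. Restate the safety power as about 88% for the planned Wilson-type interval with 84 to 85 evaluable per group, and say that it is unconditional.
3. Add the joint FAS power of the PRWE-and-safety claim: about 79% if the endpoints are independent, about 80% to 83% with test-statistic correlation of 0.3 to 0.7, and at most about 88%.
4. Note that the PP requirement can only reduce this, and that the MRI test is reached only with the resulting probability.

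The cost is a text correction and slightly less favourable figures. Sample size, margins, tests and claim rule stay as they are.

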### Magnetic resonance imaging (MRI) group of the trial

Twenty randomized patients from the centers located in or near Hanover – 10 patients with titanium screws and 10 patients with MAGNEZIX® CS – will additionally receive MRI imaging 6 weeks, 3, 6 and 12 months after randomization. MRI scans will be performed on a 3 T scanner located within the MHH.

The scanning protocol will include the following sequences: proton density weighted (PDw) turbo spin echo (TSE) fat saturated (FS) sequences in coronal and axial planes (slice thickness ≤ 2 mm), T2w TSE coronal (1 mm, without FS) and sagittal (≤2 mm, FS), T1w TSE coronal (≤2 mm, without FS) and a T1w TSE oblique sagittal sequence (1 mm, without FS) adjusted to the scaphoid bone. There will be no gap between the slices and the field of view (FOV) will not exceed 10 × 10 cm. No intravenous contrast agent will be used. All images will be viewed in a preset window-level and width with the following values for window center and width (C/W): PDw TSE/T1w 650/1300; PDw WARP 400/800.

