If non-inferiority has been established, superiority will be tested in the FAS based on the ITT population for the third primary endpoint. The hypothesis for the third primary endpoint is that the mean change in artifact size in MRI between 1-year follow-up and baseline in the magnesium-based group is different from the mean change in artifact size in MRI between 1-year follow-up and baseline in the titanium group. Superiority will be tested at the two-sided 5% test level. The Welch-type t-test will be used for judging superiority at the two-sided 5% test-level.

All secondary endpoints will be tested by appropriate tests and models exploratorily using the two-sided 5% significance level without adjustment for multiple testing.

Missing values for the primary endpoints will be imputed using MICE [46]. Missing data of scores from questionnaires will be handled according to the respective manual. As sensitivity analysis, a complete case analysis will be performed for the primary endpoints.

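### The fallback powers for the MRI endpoint match a normal approximation; the planned Welch test gives about 51% and 74%, not 56.41% and 80%

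*Protocol article*

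**What the plan says.** The MRI part comprises "10 patients with titanium screws and 10 patients with MAGNEZIX® CS". For the analysis, the article's section on statistical analysis states: "The Welch-type t-test will be used for judging superiority at the two-sided 5% test-level".

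The section on sample size calculations says that power for "the change in artifacts endpoint is virtually 100% under the following assumptions: type I error level 0.025 one-sided". The remaining inputs are "expected difference between titanium and magnesium-based screws: Δ_1_ = 3.0", a common SD of 1.0, and "drop-out 10%, effective sample size per group: *n*_*A*_ = *n*_*B*_ = 9". Two less favourable scenarios follow. One reads "The power is 56.41% if the mean difference is" 1.0, and the other gives roughly 80% at a difference of 1.32.

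The same section then justifies the planning difference. It cites artifact sizes of 8.4 ± 0.7 mm (magnesium) and 12.9 ± 1.0 mm (titanium), assumes that the magnesium artifact halves and that the titanium artifact shrinks by 1.0 mm, and concludes "so that the difference is 3.4 mm, which is rounded to 3 mm". On variability it says that, for want of further data, "we assume a common standard deviation of 1 mm, which is the standard deviation in the titanium group".

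**The concern.** With 9 patients per arm the choice between a normal and a t reference distribution matters. The two-sided 5% critical value is 1.96 for the normal and 2.12 for t with 16 degrees of freedom. If the stated powers use the first while the planned test uses the second, they are too high.

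The planning effect of 3 mm rests on an assumed halving of the artifact. The 1.0 mm and 1.32 mm figures are therefore all that the article offers a reader who asks what happens if degradation is slower. They also imply the smallest difference that the MRI part can detect with 80% power. In addition, the 3.4 mm figure does not follow from the numbers printed just before it.

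**Working it through.** **Inputs**, all from the protocol article: 9 evaluable per arm, common SD 1.0 mm, one-sided 2.5% (critical value as for two-sided 5%), differences of 1.0, 1.32 and 3.0 mm, Welch test.

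**Step 1: reproduce the stated figures.** The standard error of the difference is 1.0 × √(2/9) = 0.4714. Normal-approximation power is Φ(Δ/0.4714 − 1.96).

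- Δ = 1.0: Φ(2.121 − 1.960) = 56.41% (stated: 56.41%)
- Δ = 1.32: Φ(2.800 − 1.960) = 79.96% (stated: about 80%)
- Δ = 3.0: above 99.99% (stated: virtually 100%)

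**Step 2: rule out other routes to 56.41%.**

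| Method | 1.0 mm | 1.32 mm |
|---|---|---|
| Normal, 9 per arm | 56.41% | 79.96% |
| Normal, 10 per arm | 60.88% | 83.93% |
| Pooled t, 10 per arm | 56.20% | 79.71% |
| Pooled t, 9 per arm | 51.34% | 74.83% |

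Only the first row gives 56.41%. The third row comes close, but it misses the second decimal and contradicts the stated effective size of 9.

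**Step 3: power of the planned test.** The pooled t-test has an exact answer from the noncentral t distribution with 16 degrees of freedom, noncentrality Δ/0.4714 and critical value 2.12. The Welch test, which has somewhat fewer effective degrees of freedom, was simulated with 1,000,000 replicates per scenario (Monte Carlo error about 0.05 points).

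| Difference | Stated | Pooled t (exact) | Welch (simulated) | Stated minus Welch |
|---|---|---|---|---|
| 1.0 mm | 56.41% | 51.3% | 50.6% | 5.8 points |
| 1.32 mm | about 80% | 74.8% | 74.2% | 5.8 points |
| 3.0 mm | virtually 100% | above 99.99% | above 99.99% | none |

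**Step 4: difference needed for 80% power.**

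- Normal approximation: (1.960 + 0.842) × 0.4714 = 1.32 mm, the article's value
- Pooled t-test: 1.407 mm, about 1.41 mm
- Welch test: simulated power is 79.6% at 1.41 mm and 80.2% at 1.42 mm, so about 1.42 mm

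**Step 5: derived planning difference.** Halving 8.4 mm is a reduction of 8.4/2 = 4.2 mm. Subtracting the 1.0 mm titanium reduction leaves 3.2 mm, not 3.4 mm. Both round to 3 mm, and only 3.0 enters the power calculation.

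**The case against.** The strongest counter-argument is that nothing was decided on these figures. The MRI part is planned on 3.0 mm, and the 1.0 and 1.32 mm scenarios set no sample size, margin or decision rule. That stands, and it keeps the severity low. It does not make the printed figures right: a power quoted to two decimals for a primary endpoint should be that of the planned test.

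A second argument is that 51% and 74% are themselves conditional. They hold for a common SD of exactly 1.0 mm and 9 complete cases per arm, whereas the article also plans multiple imputation for the primary endpoints. If the SDs of change were 1.0 and 0.7 mm, Welch power would be about 62.5% and 85%, above the stated values. This also stands as a limit. The comparison here is between the stated figures and the planned test under the article's own assumptions, and the article itself sets the effective size at 9.

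Two stronger readings are tempting, and the document supports neither.

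- *A reader might infer that the MRI part is underpowered.* It is not under the planning assumptions: power at 3.0 mm is virtually 100% with either method.
- *A reader might infer that the 1 mm SD is an error, because it comes from single measurements while the endpoint is a change.* The article states 1 mm openly as an assumption made for lack of data. Whether the SD of change is larger or smaller depends on a within-patient correlation that the article does not give, and a high correlation would raise power. Nor does 1 mm amount to a correlation of 0.5 in both arms. For magnesium (SD 0.7, taken as equal at both times), 0.7 × √(2(1 − ρ)) = 1.0 gives ρ of about 0. So this is a disclosed assumption, not a wrong figure.

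**Conclusion.** The point holds as a correction of stated figures. With SD 1.0 mm in both arms, 9 evaluable patients per arm and a two-sided 5% Welch test, power is about 51% at 1.0 mm and 74% at 1.32 mm. The article's figures are 5 to 6 points too high, and its 80% point is about 0.1 mm too small (1.32 against 1.42 mm). That they come from a normal approximation is an inference, though a firm one given the match to two decimals.

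The 3.4 mm figure is a plain subtraction slip without consequence after rounding. The main power statement and the 10 per arm are unaffected. Severity is low.

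**What to change.** In the sample size section:

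- Replace the two fallback powers with about 51% at 1.0 mm and about 74% at 1.32 mm. Give about 1.42 mm as the difference with 80% power, naming the Welch test, 9 per arm and a common SD of change of 1 mm. If the pooled t-test is used for planning instead, label it so and give 51.3%, 74.8% and 1.41 mm.
- Correct 3.4 mm to 3.2 mm in the derivation. The rounding to 3 mm stays.

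The SD assumption can stay as disclosed. The cost is a few restated figures, with no change to design, sample size or analysis.

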### Data management and data monitoring

Database and eCRF are developed, maintained and hosted by AMEDON GmbH. AMEDON GmbH will also perform data management. The trial database has been developed and validated before data entry based on standard operating procedures (SOPs). All changes made to the data are documented in an audit trail. The trial software has a user and role concept that can be adjusted on a trial-specific basis. The database is integrated into a general information technology infrastructure and safety concept with a firewall and backup system. The data are backed up daily. After completion and cleaning of data, the database is locked, and the data are exported for statistical analysis.

The data will be entered via the internet at the trial sites. Plausibility checks are run during data entry, thereby detecting many discrepancies immediately. Data management and monitoring will conduct further checks for data completeness and plausibility of data, and they will clarify any questions with the trial sites. These queries must be answered by the trial site without unreasonable delay. Further details are specified in the Data Validation Plan and in the Monitoring Manual.

Data management will be performed in compliance with AMEDON GmbH and in accordance to EN 14155 [49].

All relevant study data will be stored by the sponsor of the study. In the individual participating centers, the investigator files, study-related correspondence, patient identification list, consent forms and patient files will be retained for at least 10 years after the end of the study. Other in-house regulations or legislations demanding longer retention periods (e.g. radiation control regulation, radiation protection law) will be respected.

AMEDON GmbH is responsible for clinical onsite monitoring according to EN14155, written SOPs and the monitoring manual to ensure patient’s rights, patient’s security and reliability of trial results. For initiation, the trial site will be visited onsite by a clinical research associate. During the trial, sites will be visited at regular intervals depending on the rate of recruiting and data quality.

No audits are planned. However, to ensure correct execution of the study, audits may be conducted if necessary.

The trial is under medical direction. All staff members underlie medical confidentiality. Within a first training of staff and additional, consistently occurring staff trainings, the authorized clinic staff in the study sites will be instructed to handle all data as well as project-specific contents confidentially and to use all regular protection measures (recent version of antivirus-software, computer blocking by leaving the room, logout from eCRF after successful data transfer etc.).

